# Effects of Transcranial Direct Current Stimulation on Knee Osteoarthritis Pain in Elderly Subjects With Defective Endogenous Pain-Inhibitory Systems: Protocol for a Randomized Controlled Trial

**DOI:** 10.2196/11660

**Published:** 2018-10-29

**Keywords:** transcranial direct current stimulation, elderly, chronic pain, knee osteoarthritis, conditioned pain modulation

## Abstract

**Background:**

Knee osteoarthritis (OA) has been the main cause behind chronic pain and disabilities in the elderly population. The traditional treatment for knee OA pain currently concerns a number of combinations of pharmacological and nonpharmacological therapies. However, such combinations have displayed little effects on a significant group of subjects. In addition to this, pharmacological treatments often cause adverse effects, which limits their use on this population. Previous studies showed that chronic knee OA pain may be associated with maladaptive compensatory plasticity in pain-related neural central circuits indexed by a defective descending pain-inhibitory system. Transcranial direct current stimulation (tDCS) can revert some of these maladaptive changes, thus decreasing chronic pain sensation. Numerous studies have demonstrated that the use of anodal tDCS stimulation over the primary motor cortex (M1) has positive effects on chronic neuropathic pain. Yet, data on OA pain in elderly patients, including its effects on the endogenous pain-inhibitory system, remain limited.

**Objective:**

The objective of this study is to evaluate the efficacy of tDCS in reducing pain intensity caused by knee OA in elderly subjects with defective endogenous pain-inhibitory systems.

**Methods:**

We designed a randomized, sham-controlled, single-center, double-blinded clinical trial. Patients with knee OA who have maintained a chronic pain level during the previous 6 months and report a pain score of 4 or more on a 0-10 numeric rating scale (NRS) for pain in that period will undergo a conditioned pain modulation (CPM) task. Participants who present a reduced CPM response, defined as a decrease in NRS during the CPM task of less than 10%, and meet all of the inclusion criteria will be randomly assigned to receive 15 sessions of 2 mA active or sham tDCS for 20 minutes. A sample size of 94 subjects was calculated. The Brief Pain Inventory pain items will be used to assess pain intensity as our primary outcome. Secondary outcomes will include pain impact on functioning, mobility performance, quality of life, CPM, pressure pain threshold, touch-test sensory evaluation, and safety. Follow-up visits will be performed 2, 4, and 8 weeks following intervention. The data will be analyzed using the principle of intention-to-treat.

**Results:**

This study was approved by the institutional review board with the protocol number 1685/2016. The enrollment started in April 2018; at the time of publication of this protocol, 25 subjects have been enrolled. We estimate we will complete the enrollment process within 2 years.

**Conclusions:**

This clinical trial will provide relevant data to evaluate if anodal tDCS stimulation over M1 can decrease chronic knee OA pain in elderly subjects with defective CPM. In addition, this trial will advance the investigation of the role of central sensitization in knee OA and evaluate how tDCS stimulation may affect it.

**Trial Registration:**

ClinicalTrials.gov NCT03117231; https://clinicaltrials.gov/ct2/show/NCT03117231 (Archived by WebCite at http://webcitation.org/73WM1LCdJ)

**International Registered Report Identifier (IRRID):**

RR1-10.2196/11660

## Introduction

Osteoarthritis (OA) is the most common cause of pain and disabilities in elderly populations, and the knee is the most commonly affected joint [1,2]. OA is a disease characterized by cell stress and extracellular matrix degradation that stimulates maladaptive repair responses as proinflammatory pathways of innate immunity [3]. It has been determined that 33.6% of individuals older than 65 years suffer from OA, and 10% of individuals aged 60 years and older have symptomatic knee OA [4]. Subjects with chronic knee OA pain may experience depressive symptoms, sleep disorders, functional dependency, and a decrease in life quality, and this can have a subsequent impact on public health system costs [5]. OA knee pain is traditionally managed with a combination of pharmacological and nonpharmacological therapies including weight loss, physical therapy, several exercise modalities, anti-inflammatory drugs, topical agents, and opioids analgesics [6]. Although these treatments can decrease the pain intensity, they can also lead to substantial adverse effects (eg, dizziness, dry mouth, constipation, and nausea), and the treatment benefits may decrease over time (eg, opioid tolerance development) [7-9]. Previous studies suggested that peripheral and central sensitization are two of the underlying mechanisms in OA pain that can lead to lower pain thresholds, hyperalgesia, and spatial summation in asymptomatic areas [10,11].

Peripheral sensitization is caused by changes in the physiology of peripheral nociceptors due to localized inflammation. At the central level, there is an imbalance in endogenous pain modulation, characterized by a greater facilitation of pain and a reduced capacity to inhibit pain [12]. In addition, the aging process is associated with a dysregulation in the central modulation of pain, potentially placing elderly patients at a greater risk of chronic pain [13,14]. Conditioned pain modulation (CPM) is one of the most studied dynamic quantitative sensory tests; CPM is related to the reduction of pain produced by a test stimulus in response to a second noxious conditioning stimulus on a remote body side [15-17]. Previous studies showed that the pain reduction during CPM testing in healthy adults is approximately 23%, while in the healthy elderly population the reduction is approximately 17% [18,19]. A recent study indicated that elderly individuals with chronic pain due to severe osteoarthritis may have a significant dysfunction in the descending control of nociceptive processing, as the pain reduction during a CPM task is less than 10% [20].

In support of the above mentioned central sensitization mechanism, the rationale for treatment should also aim to modulate central nervous system plasticity [21,22]. Although drugs can change brain plasticity, their effects are more diffuse, which limits results. Moreover, as pharmacological treatments to chronic pain often lead to intolerable side effects in elderly patients, there is an increasing interest in nonpharmacological intervention options [23-25]. Transcranial direct current stimulation (tDCS) is a powerful noninvasive technique to modulate cortical excitability using a weak direct current applied through the scalp in a painless way; its prolonged and continuous application can induce neuroplasticity [26,27]. These changes depend on the polarity of the montage, with anodal stimulation enhancing excitability and cathodal stimulation decreasing excitability [28]. tDCS has shown positive effects on chronic pain in some diseases, which indicates that it may revert maladaptive plasticity associated with chronic pain sensation [29,30]. For pain, the most effective cortical target is the primary motor cortex (M1), a gateway to deep pain-related networks such as thalamic nuclei [31,32]. Previous brain imaging studies showed a positive cortical and subcortical neurophysiologic response to tDCS with anode over M1 and cathode over contralateral supraorbital region [33,34]. A recent trial showed that tDCS over the motor cortex might increase CPM response [35]. Another recent pilot trial evaluated the effect of tDCS on clinical pain severity for older adults with knee OA; it did not display consistent results in all pain assessments, yet their preliminary results showed promising clinical efficacy [36].

The aim of this trial is to assess the effects of tDCS on the intensity of pain in elderly patients suffering with OA knee chronic pain. We chose to test these effects in aged people with defective endogenous inhibitory pain systems, as the previous data showed increased therapeutic response in this population [37,38]. As secondary outcomes, we will evaluate the safety of tDCS and the changes in quality of life, pain impact on functioning, CPM, pressure pain threshold, touch-test sensory evaluation, and mobility performance.

## Methods

### Study Design

We will conduct a single-center, double-blinded, randomized, and controlled parallel clinical trial. The study was approved by the Ethics Committee of São Paulo Hospital (HSP) with the protocol number 1685/2016 and has been registered with ClinicalTrials.gov (NCT03117231). The trial will be performed at the Federal University of São Paulo, Brazil, and will be reported according to the Consolidated Standards of Reporting Trials (CONSORT) [39]. Participants will agree to the participation by signing the informed consent. They will be allowed to leave the study at any time without negative repercussions.

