### Participants

Individuals aged 60 years and older, which is the definition for the elderly in Brazil [40], with an established diagnosis of unilateral or bilateral knee OA as established by the American College of Rheumatology criteria of 1986, using history, physical examination, and radiographic findings according to the Kellgren-Lawrence radiographic grading, will be recruited [41]. Patients will be recruited from HSP and from all the outpatient clinics belonging to the Federal University of São Paulo. Eligible subjects will have had pain in the knee for a minimum of 6 months, with an average pain score of 4 or more on a 0-10 numeric rating scale (NRS) for pain over that period and during the week prior to the first stimulation session. Following this, the subjects will be required to report a reduction on NRS during the CPM task of less than 10% compared to the pain score before the test.

Exclusion criteria include patients who have any severe acute or chronic uncompensated disease (such as uncontrolled hypertension, diabetes, cardiac issues, heart failure, or chronic obstructive pulmonary disease), history of epilepsy or syncope, contraindications to transcranial brain stimulation (ie, implanted brain medical devices or implanted brain metallic devices), established cognitive impairment, history of fractures in the lower limbs and/or spine in the last 6 months, traumatic brain injury with residual neurological deficits, alcohol abuse within the last 6 months as self-reported, use of carbamazepine within the last 6 months as self-reported, or severe depression (with a score of more than 30 on the Beck Depression Inventory). The principal investigator will obtain informed consent prior to enrolling participants in the study. We expect in this elderly population to have a female-to-male ratio of about 70%:30%.

In order to avoid drop outs, the principal investigator will follow up with all participants by phone during the entire study to remind them of the schedule. Participants and treating physicians will be told that changes in treatment during the study are strongly discouraged and must be reported. In addition, no treatment crossover will be permitted.

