### Intervention

The treatment will be administered for 3 weeks with intervention sessions daily from Monday to Friday for a total of 15 days of electrical stimulation [37]. The participants will not receive cash, reimbursements, food, transportation, or any compensation for their participation in the trial. After the initial assessment and before randomization, the subjects will be informed about the possible sensations with the stimulation and instructed not to reveal the sensation experienced.

Participants will be seated comfortably in an armchair while receiving tDCS. All subjects will receive 20 minutes of either sham or active tDCS, using a pair of 35 cm^2^ surface sponge electrodes soaked with physiologic saline and fixed to the head with elastic bands. The transcranial stimulation will be applied by a constant current device (Soterix 1×1 Low-Intensity Stimulator, Soterix Medical Inc) with an intensity of 2 mA. A gradual current ramp-up and ramp-down with 30-second durations will be used. The anode will be placed over C3/C4 (International 10-20 electroencephalogram system), which corresponds approximately to the location of M1 of the contralateral side to the most affected knee. The cathode electrode will be placed over the contralateral orbital, meaning ipsilateral to the most affected knee. The tDCS will be administered by a physician with specific training is this modality of intervention.

Sham tDCS stimulation will look and feel exactly the same as the active stimulation; however, the stimulator will deliver 2 mA of current for only 30 seconds. This sham stimulation method is frequently used and has been shown to be reliable [42].

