### Outcome Measurements

Following determination of participant eligibility and obtaining informed consent, we will collect baseline information about the subjects through a structured interview. Collected data will include sociodemographic information, mood and cognitive evaluation, radiographic data, and clinical history. We will perform all assessments during the baseline visit to obtain data to compare with the follow-up visits. Baseline data will be collected 1 week prior to the beginning of treatment. After 3 weeks of intervention, we will evaluate the participants over the course of 2 months, with 3 follow-up visits during this period (see Figure 1 for flow diagram). These outcome time points were chosen based on tDCS trials to assess early and late effects [27,36,37].

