### Primary Outcome

We will analyze pain intensity in the previous 24 hours using the Brief Pain Inventory (BPI); this is a short, self-report questionnaire [43]. The BPI includes 4 items that measure pain intensity (pain right now, pain on average in last 24 hours, worst pain in last 24 hours, and least pain in last 24 hours) using an NRS from 0 (no pain) to 10 (pain as bad as you can imagine). The mean of these 4 pain items will be used as our primary outcome. The BPI also includes 7 items that assess the impact of the pain on functioning using a 0 (no interference) to 10 (complete interference) rating scale, which will be used as a secondary outcome.

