### Sample Size and Data Analysis

The sample size was estimated using the minimal clinically important difference (20% reduction from the baseline) in the outcome of pain intensity measured by the NRS as a parameter. The effect size and the probability of error type I (alpha) and type II (beta) were 0.59, .05, and .2, respectively. According to the sample calculation, that total size would be 94 participants. We will increase the sample size by 10% to account for dropouts and other unexpected factors. Thus, the final sample size is 104 subjects.

All analyses will be conducted according to the principle of intention-to-treat (ITT) using a regression-based single imputation method. The ITT population will include all randomized subjects. We will perform an additional sensitivity analysis in which we will use the method of multiple imputation. Initially, the baseline characteristics between sham and tDCS groups will be tested using Student *t* tests; to analyze our primary outcome, which is pain intensity measured by BPI, we will adopt a mixed analysis of variance model in which the dependent variable will be the outcome (BPI) and the independent variables will be group (tDCS-a or tDCS-s), time (baseline and after treatment and follow-up), and the interaction group time. Secondary analyses will be conducted in an exploratory manner (no correction for multiple comparisons). Similar analysis will be conducted for the adverse effects measuring continuous outcomes, and for the categorical outcomes, we will use Fisher exact tests. In both cases, for the safety analysis, we will use uncorrected *P* values to increase the likelihood of detecting detrimental adverse effects.

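### The two named missing-data analyses, as normally run, share one assumption, and the planned phone calls are not used to collect the four-item primary outcome

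*Protocol article*

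**What the plan says.** The Sample Size and Data Analysis section includes every randomized participant under intention-to-treat and fills gaps by regression-based single imputation. It names one check: "We will perform an additional sensitivity analysis in which we will use the method of multiple imputation". It gives no imputation model, list of predictors or departure from missing at random. The same section adds 10% to the sample size for dropouts and other unexpected factors.

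Under Participants, the contact plan is that "the principal investigator will follow up with all participants by phone during the entire study to remind them of the schedule". The stated aim is to avoid dropouts, and collecting outcomes is not mentioned. Under Primary Outcome, the BPI pain items are four self-reported 0-10 ratings: "The mean of these 4 pain items will be used as our primary outcome".

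Attendance is demanding. The Intervention section sets "intervention sessions daily from Monday to Friday for a total of 15 days of electrical stimulation" and adds: "The participants will not receive cash, reimbursements, food, transportation, or any compensation for their participation in the trial". After treatment, "we will evaluate the participants over the course of 2 months, with 3 follow-up visits during this period" (Outcome Measurements). On leaving, Study Design says only: "They will be allowed to leave the study at any time without negative repercussions".

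**The concern.** The participants are aged 60 or over, have painful knees, and must travel to many visits without transport or reimbursement. Some will miss visits, and they may differ in pain from those who keep attending, for example because they had no relief or tolerated the sessions poorly. Regression imputation predicts their pain from patients who were observed. Standard multiple imputation does the same and adds the uncertainty of the prediction. It repairs the standard error but does not test whether leavers resemble stayers. If they do not, and the arms differ in how many leave or in how far leavers fall short, the treatment effect is biased. Both named analyses would then show the same bias, and a reader could take their agreement as reassurance.

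Part of the gap could be closed by observing the outcome. Nothing in the article's description of the four BPI pain items requires a clinic visit, and phone contact with every participant is already planned.

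**Working it through.** **The plan's own figures.** With effect size 0.59, two-sided alpha 0.05 (the article does not state sidedness), 80% power and 1:1 allocation, the t-based solution is 46.08 per arm. That rounds up to 47, giving 2 x 47 = 94 as stated. Then 94 x 1.10 = 103.4, rounded up to 104, or 52 per arm. The allowance is therefore about 10 patients.

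**Bias formula.** Let p be the share missing in an arm, and let d be how much worse, in SD, its missing patients are than the imputation predicts. Then

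bias in the arm difference = p(active) x d(active) - p(sham) x d(sham).

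A positive value overstates benefit. The article gives no loss by arm and no value of d, so both are assumptions. Each row below keeps overall loss at 10%; for example, 15% and 5% of 52 are 7.8 and 2.6, together 10.4 of 104.

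| Loss, active / sham | Who falls short | Bias (SD) for d = 0.5 to 1.0 | Share of 0.59 |
|---|---|---|---|
| 10% / 10% | both arms equally | (0.10 - 0.10) x d = 0 | 0% |
| 15% / 5% | both arms equally | 0.10 x 0.5 = 0.05 to 0.10 x 1.0 = 0.10 | 8% to 17%, overstated |
| 5% / 15% | both arms equally | -0.05 to -0.10 | 8% to 17%, understated |
| 15% / 5% | active arm only | 0.15 x 0.5 = 0.075 to 0.15 x 1.0 = 0.15 | 13% to 25%, overstated |

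**Would the two analyses disagree?** This was simulated with 52 per arm, one baseline and one post-treatment value (assumed correlation 0.5). Single regression imputation was compared with multiple imputation (20 imputations), both conditioning on arm and baseline, with 1,500 runs per case. Negative values favour active, and d = 0.59 in each case.

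- 20% / 0% loss, a deliberately extreme split: the true effect is -0.59 + 0.20 x 0.59 = -0.47. Both methods return -0.59.
- 15% / 5% loss: the true effect is -0.59 + 0.10 x 0.59 = -0.53. Both methods return -0.59.
- 10% / 10% loss: the true effect is -0.59. Both methods return -0.59, so there is no bias.

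**Does phone collection help?** In the 20% / 0% case, collecting a random half of the gaps moves the estimate to -0.53. Collecting all of them gives -0.46, within 0.01 of the truth. The planned sample size does not change.

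**The case against.** A reader might infer that patients who stop sessions are treated as having left the study, so that their pain is always imputed. The article does not say so. The sentence in Study Design is an ordinary consent right. Intention-to-treat on everyone randomized, phone contact throughout the study and follow-up visits described without exceptions are all compatible with continued assessment. A condensed article may leave the rule on stopping sessions versus withdrawing to the full protocol, so its absence is not a finding by itself.

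A reader might also infer that no planned analysis could detect the bias. That too goes beyond the text. The multiple imputation is not specified further and could contain a delta adjustment. Adverse effects and mood are recorded at every session (Adverse Effects section), and earlier BPI scores may exist for late leavers. If these entered the imputation model, they could reduce the shortfall.

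The size and direction of bias are also assumed. If lack of relief drives leaving and the stimulation works, sham could lose more patients, and the bias would run against the treatment. Finally, the planned calls are made by the principal investigator rather than a blinded evaluator, and some leavers will refuse contact or be unreachable.

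All of this stands and narrows the point. It does not remove two stated choices: the only sensitivity analysis named is one that normally shares the primary method's assumption, and the planned calls have only a reminder purpose.

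**Conclusion.** The point holds in a limited form. As normally run, regression-based single imputation and multiple imputation rest on the same missing-at-random assumption, so their agreement would not reveal informative dropout. A feasible way of observing the primary outcome for people who miss visits is not used in the plan as described.

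With about 10% missing, the bias ranges from zero (equal loss and equal shortfall) to 0.05-0.10 SD in either direction (a 15% versus 5% split, with a shortfall of 0.5-1.0 SD in both arms). It reaches 0.075-0.15 SD if only the active-arm leavers (15%) fall short. These figures depend wholly on assumed loss by arm and assumed shortfall. They show what could go unnoticed and do not predict what will happen.

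**What to change.** In the Participants section, extend the purpose of the phone contact. When a visit is missed and the participant has not refused contact, a blinded evaluator asks the four BPI pain items by phone at the scheduled time point and records the mode of collection. In Sample Size and Data Analysis, state that these values enter the primary intention-to-treat analysis. For values still missing, make the multiple-imputation sensitivity analysis delta-adjusted: shift the imputed scores by stepped amounts, separately in each arm, until the conclusion changes, and report that point.

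The cost is a short amendment, a few calls made by a blinded evaluator instead of the principal investigator, and slightly more analysis work. A few primary values will come by a different mode, and not every leaver will be reached. The Results section reports 25 of the planned 104 included and 10 completed at publication, so most outcome data could still benefit.
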